**Figure 1 Fig1:**
[figure not shown]
**Flow chart of the study.**

Infants assigned to the study group will be further randomly divided into: OMT group A and OMT group B (Figure 1).

The coordinating centre will perform and store the randomisation list and an external consultant will be in charge of the process. NICU personnel will be unaware of outcome, study design and patients’ allocation. Only osteopaths will be aware of patients’ allocation.

### Osteopathic procedure

Osteopathic care includes an initial structural evaluation and a final treatment. The structural evaluation is carried out with the newborn lying down in bed and is aimed at diagnosing somatic dysfunctions [19]. The osteopathic manipulative treatment includes the application of a range of manipulative techniques aimed at treating the somatic dysfunctions. Techniques chosen for the present study are balanced ligamentous/membranous tension techniques [15]. The whole session will last 30 minutes: 10 minutes for evaluation and 20 minutes for treatment [15].

OMT will be performed by registered osteopaths with experience in the neonatology field (OMT group A) and final-year students (OMT group B). Newborns allocated to the study group will undergo osteopathic care in addition to usual care.

The sham group will receive only ‘soft touch’, for 30 minutes, plus routine care, whereas the control group will receive routine care only.

Osteopathic care and sham therapy will be administered once a week according to the treatment group. OMT groups A and B will enter the NICU on different days of the week.

### Data entering and data export

Data will be collected using an *ad-hoc* platform already used in previous studies [13,20,21]. Medical records will be acquired daily by the NICU staff.

Osteopathic records will be reported once a week when the osteopathic service is provided.

Maternal data will be also include collecting the following information: type of delivery, foetal presentation, whether placental abruption, pregnancy complications, single versus multiple gestation, whether premature rupture of membranes and any other complication.

Neonatal data will be gathered using the following parameters: gender, GA, birth weight, infants small for GA, neonatal complications (diagnosed at birth and during hospitalisation), diagnosis-related group (DRG) at discharge and reasons for drop out, if any.

A monitoring board will be organised and periodically will review the safety of data according to survival rate at discharge and relative risk of developing any clinical complication. The group sequential method will be utilised to define the rate at which type I errors occur; the Lan-DeMets generalisation of the O’Brien-Fleming boundary will be chosen. Interim analyses will be performed. Moreover, the monitoring board will be in charge of data export.

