**Methods/design:**

A three-armed single blinded placebo-control randomised controlled trial protocol has been designed to primarily evaluate the extent to which OMT is effective in reducing pain in preterms. One hundred and twenty newborns will be enrolled from one tertiary neonatal intensive care unit in central Italy and randomised in three groups: study, sham and control. The study group will be further prospectively randomised in two subgroups: experienced osteopaths and students. All preterms will receive standard medical care. Osteopathic treatment will be applied to the study group only whilst ‘soft touch’ will be administer to the sham group only. Newborns will undergo manual sessions once a week for the entire period of hospitalisation. Blinding will be assured for neonatal staff and outcome assessor. Primary outcome will be the mean difference in baseline score changes of PIPP questionnaire between discharge and entry among the three groups. Secondary outcomes will be: mean difference in length of stay and costs between groups. Statistical analyses will use per-protocol analysis method. Missing data will be handled using last observation carried forward imputation technique.

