### Randomisation and masking

Patients will be randomly assigned in a 1:1:1 ratio to either the OMT, the sham or the control group (Figure 1). Newborns will be eligible for randomisation from the first day of life. Block randomisation will be performed according to a computer-generated randomisation list using a block size of nine, and stratified by OMT group.

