### Measures

The PIPP is a seven-item multidimensional (composite) measure of pain, largely used to assess acute pain in infants [11] and extensively validated for both preterm and term newborns [22]. Items are empirically and theoretically derived and are categorised as: contextual ((GA) and behavioural state (BS)), physiological (heart rate and oxygen saturation) and behavioural (facial actions). Numeric scores, reflecting baseline changes and based on an empirically 4-point scale (0, 1, 2, and 3), are provided for physiological and behavioural items. Conversely, the contextual items (GA and BS) have a reversed score (3, 2, 1, and 0) accounting for physiological differences related to prematurity. The maximum PIPP score is 21 for infants < 28 weeks GA and 18 for full-term newborns.

Considering LOS, according to international guidelines, well-determined discharge parameters are required and listed as follows: coordinated breathing, swallowing and sucking while feeding; stability of cardiorespiratory function; sustained weight gain and body heat at room temperature [23].

Regarding NICU costs, costs per day are calculated according to local authorities, multiplied by the days of hospitalisation. Costs are estimated in euros per day.

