### Cost analysis

Ordinary least squares regression will be performed to quantify the cost of hospitalisation among preterms after adjusting for gender, GA, LOS, birth weight, OMT, time to first OMT, and DRG. Cost data is extracted from 2014 to 2015 administrative databases of the Regional Office of the Ministry of Health of Abruzzo where the NICU of the present RCT is located.

To calculate the precise cost, the reimbursement allocated to each DRG from the Istituto Superiore di Sanità (National Healthcare Institute) is used. Specifically DRGs and reimbursements considered are 386 (€12.932.69), 387 (€7.450.09) and 388 (€3.757.22) [25].

As for the study group, OMT costs are theoretically set at €20.00 considering fees from health insurance companies [26].

Cost estimates will be adjusted for inflation to 2014 euro value using the Medical Component of the Consumer Price Index.

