### Ethics

The approval of the Ethics Committee of the local health agency of Pescara (number 78/2013) has been obtained and the protocol has been registered on ClinicalTrials.gov (NCT02146677) on 20 May 2014. No disadvantages for the intervention are expected and no possible adverse events and side effects owing to OMT are predicted as confirmed by the recent osteopathic literature [13,15]. In any case, side effects and reason for drop out will be recorded during the research period and discussed in the final paper.

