## Discussion

The present single blinded RCT has been designed to explore potential advantages of OMT in the management of newborns’ pain. Currently, based on a patient-centred need-based approach, this research will be looking at the benefit of OMT rather than the efficacy of a specific technique or a pre-determined protocol. Moreover, it will attempt to confirm the effectiveness of OMT on LOS-shortening using a larger experimental study design and to corroborate the absence of placebo effects in newborns. Furthermore, it will explore potential differences between expert osteopaths and final-year students on the effectiveness of OMT.

To date, no osteopathic trial has been carried out in this field attempting to quantify the benefits of OMT in newborns’ pain using rigorous procedures and ‘gold-standard’ methods for clinical trials. This will be the first concrete experimental trial addressing this outcome. The expected advantages from the present trial will be reduction of pain, shorter LOS and lower neonatal costs in the OMT groups compared to sham and control groups.

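### The board's safety comparison stops at discharge, which the trial expects OMT to bring forward, so a simple in-hospital relative risk leans towards OMT looking safe by an amount the article does not let us derive

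*Protocol article*

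**What the plan says.** Under Data entering and data export, the monitoring board will periodically "review the safety of data according to survival rate at discharge and relative risk of developing any clinical complication". The same section lists the neonatal data, including "neonatal complications (diagnosed at birth and during hospitalisation" and then other items. Survival and collected complications are therefore both observed up to discharge.

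Outcomes lists a between-group difference in the risk of adverse events and side effects, with no time horizon. It also lists length of stay as a comparison between the three groups. The Discussion states the direction hoped for: "The expected advantages from the present trial will be reduction of pain, shorter LOS and lower neonatal costs in the OMT groups", compared with sham and control.

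Four other statements bear on the point:
- Ethics: "side effects and reason for drop out will be recorded during the research period". That period is not defined for the individual infant.
- Abstract, Methods/design: "Newborns will undergo manual sessions once a week for the entire period of hospitalisation". Exposure to treatment therefore also ends at discharge.
- Measures: discharge depends on clinical criteria, among them "stability of cardiorespiratory function; sustained weight gain and body heat at room temperature".
- Cost analysis: "Cost data is extracted from 2014 to 2015 administrative databases of the Regional Office of the Ministry of Health of Abruzzo".

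**The concern.** A risk compares like with like only when each arm is observed for the same length of time. Here the end of observation is discharge, and the trial's own hypothesis is that discharge comes sooner with OMT. The arm that goes home earlier has fewer days in which a death or complication can be counted, even if treatment has no effect on either. The bias therefore favours OMT exactly when OMT succeeds on length of stay.

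Two uses of the data are affected. The board would be reviewing a measure that can understate harm while the trial runs. The final report could set a shorter stay and lower cost beside no excess of complications, although deterioration after an earlier discharge lies outside the window in which survival and complications are collected.

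**Working it through.** **Figures in the article.** No figure is given for safety. The only design calculation is for the primary outcome: f = 0.30, power 0.80 and alpha 0.05, giving 37 per group. For a three-group ANOVA using the noncentral F with λ = N·f², power is 0.792 at 36 per group and 0.803 at 37, so 37 is reproduced. The present point does not depend on it.

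**Inputs.** From the article: a window ending at discharge, a shorter stay expected with OMT, and 40 infants per group. Assumed, because the article does not give them: the comparator's complication risk, the fractional reduction in stay s, and the shape of the hazard over the stay.

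**Constant hazard.** Let H be the comparator's cumulative hazard over its stay and k the true ratio of daily rates, OMT to comparator. The OMT risk is 1 − exp(−k·H·(1 − s)) and the comparator risk is 1 − exp(−H).

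Take 1% per day and a 25-day comparator stay, so H = 0.25 and the risk is 0.2212. With k = 1 (no true effect):
- 22.5 days: 0.2015, relative risk 0.91
- 20 days: 0.1813, relative risk 0.82
- 17.5 days: 0.1605, relative risk 0.73

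Varying the comparator risk, still with no true effect:

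| Comparator risk | Stay 10% shorter | 20% shorter | 30% shorter |
|---|---|---|---|
| 10% | 0.90 | 0.81 | 0.71 |
| 20% | 0.91 | 0.82 | 0.72 |
| 40% | 0.92 | 0.84 | 0.75 |

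The relative risk equals 1 when k = 1/(1 − s), that is 1.11, 1.25 or 1.43 for stays 10%, 20% or 30% shorter. Smaller harms look protective and larger ones are attenuated. For example, with comparator risk 20% and s = 0.20, k = 1.5 gives a risk of 0.235 and a relative risk of 1.17.

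**Hazard concentrated earlier, stay cut from 25 to 20 days, no true effect.**
- *Low-risk final days.* Hold the total at 0.250 and let each of the last five days carry one third of 1%. The days lost carry 5 × 0.01/3 = 0.0167, leaving 0.2333. The OMT risk is 1 − exp(−0.2333) = 0.2081, and the relative risk is 0.2081/0.2212 = 0.94. The rate ratio that would look neutral is 0.250/0.2333 = 1.07.
- *Half the hazard in the first 7 days, comparator risk 20%.* H = −ln 0.8 = 0.2231. The OMT infants accrue 0.2231 × (0.5 + 0.5 × 13/18) = 0.1922, a risk of 0.175 and a relative risk of 0.87.
- *90% of the hazard in the first 7 days, comparator risk 20%.* They accrue 0.2231 × (0.9 + 0.1 × 13/18) = 0.2169, a risk of 0.195 and a relative risk of 0.98.

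**Power to see harm.** With 40 per arm, comparator risk 20% and a doubled daily rate, equal observation gives an OMT risk of 1 − 0.8² = 0.36 and power of about 36% (two proportions, two-sided 5%). If the OMT stay is 20% shorter, the risk is 1 − 0.8^1.6 = 0.30 and power is about 18%.

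**The case against.** The strongest reply is that the constant hazard drives the large figures. The days lost to an earlier discharge are the last ones, when the discharge criteria are being met, and those are plausibly low-risk days. Complications diagnosed at birth cannot depend on length of stay, so counting them dilutes the effect further. A complication in hospital may also delay discharge, which offsets part of the bias. All of this stands. It reduces the size, and it is why 0.82 should not be quoted alone.

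A reader might infer that real harm would be fully masked. The documents do not support that. It needs OMT to raise the daily rate by a particular amount (25% for a stay 20% shorter under a constant hazard) and to shorten the stay as well, although discharge depends on stability and NICU staff are unaware of allocation. It is one scenario among several.

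A reader might also infer that all safety recording stops at discharge. Ethics does not say so: side effects are recorded over a research period that is not defined per infant. For the adverse-event outcome the hospital limit is an inference.

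It may further be said that a condensed article leaves follow-up windows to the full protocol or analysis plan. That would answer a complaint about missing detail. Here the article itself names the board's measures and the span over which complications are collected. A later plan could add rates, but it could not recover events after discharge that were never collected.

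Finally, with 40 per arm safety inference is weak even with equal observation. That is true, but it does not remove the direction of the bias.

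**Conclusion.** The point holds as a conditional bias. If the stay is shorter with OMT, the in-hospital comparison of survival and complications is tilted towards OMT looking safe. The direction follows from the article's own definitions and its own hypothesis. The size does not: for a stay 20% shorter and no true effect, the relative risk runs from about 0.82 (constant hazard) to about 0.94 to 0.98 (low-risk final days, or most of the risk in the first week). The comparator risk, the length of stay, the reduction in stay and the hazard shapes are all assumptions. If OMT does not shorten the stay, this bias does not arise. It merits a change of analysis wording, and a limit on what the report may claim, rather than a change of design.

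**What to change.** In Data entering and data export and in Outcomes:
- Count only complications arising after randomisation, so that birth diagnoses do not enter the comparison.
- Keep the relative risk. Beside it, give the board and the final analysis the rate per infant-day in hospital and the risk over a common early window from randomisation. Treat discharge as the end of observation, and state for each arm how many infants leave before the window closes.
- Word any statement of no excess harm as applying to the hospital stay only.
- If the regional administrative data prove linkable to individual infants, add death or readmission by a fixed time from randomisation. The article describes those databases only as a source of cost data, so this must be confirmed first and covered in the consent and the data request. If they are not linkable, state that harm after discharge was not assessed.

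The cost is a little more analysis, using records the NICU staff already acquire daily. The early window will hold few events and loses infants who leave before it ends. The per-day rate is itself affected by healthier infants leaving sooner, so it supports the risk comparison and does not replace it.

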### Outcomes

Primary outcome will be the mean difference in baseline score changes of PIPP questionnaire between discharge and entry among the three groups.

Secondary outcomes will include:mean difference in PIPP questionnaire scores before and after each treatmentmean difference in LOS measured in days between the three groupsmean difference in costs between the three groupsmean difference in PIPP questionnaire scores between the two OMT subgroupsmean difference in LOS measured in days between the two OMT subgroupsmean difference in costs between the two OMT subgroupsdifference in the risk of adverse events and side effects between the three groupsaverage daily weight gain measured in grams

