### Statistical analysis

According to Stevens *et al*. [11] the mean PIPP score for a painful procedure is 12.9 (standard deviation (SD), 3.4) and 6.0 (SD, 2.7) for a non-painful procedure. For a heel stick, the mean score is 10.3 (SD, 4.5) and 6.3 (SD, 3.2) for a simulated handling. However, as there is a lack of clinical trials in complementary medicine and/or manual disciplines, the sample size is computed considering an effect size (f) of 0.30, a statistical power of 0.80 and an α-level equal to 0.05 to produce a sample size of 37 per group. To prevent loss of power, the sample size is increased up to 40 subjects per group (total sample N = 120).

The primary analysis of the present clinical trial will be conducted according to per-protocol principle and intention-to-treat. Missing data will be handled using the last observation carried forward imputation technique. Arithmetic means and SD as well as median, percentage and range will be used to describe the general characteristics of the study population. Univariate statistical tests, Student’s *t*-test, analysis of variance (ANOVA) and chi square test, will be performed to compare the study groups and control group at the baseline. A linear mixed effect model will be used to evaluate the PIPP score across groups. Data will be analysed within and between the three study groups. Furthermore, a linear regression model will be applied to study the independent effect of OMT on primary and secondary endpoints between OMT groups A and B. Two-tailed *P*-values of less than 0.05 are considered to indicate statistical difference. To describe imbalances between groups, mean or relative risk with 95% CI will be used. Effect sizes will be computed stratifying by gestational age. R statistical programme (Vienna, Austria) will be used for data analysis [24].

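### The primary outcome is an entry-to-discharge change in PIPP with no stated adjustment for entry PIPP or gestational age; naming both as covariates would gain precision and protect against chance imbalance

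*Protocol article*

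**What the plan says.** The protocol article (Outcomes) defines the endpoint: "Primary outcome will be the mean difference in baseline score changes of PIPP questionnaire between discharge and entry among the three groups". Its Statistical analysis section gives one sentence on the model: "A linear mixed effect model will be used to evaluate the PIPP score across groups". That sentence names no covariate and does not say how the entry score enters.

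Both candidate covariates are at hand. Entry PIPP is needed to form the primary outcome. GA is on the collection list (Data entering and data export): "Neonatal data will be gathered using the following parameters: gender, GA, birth weight". Under Randomisation and masking, the list is stratified by OMT group only, not by GA or entry PIPP.

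The plan touches baseline differences in three other ways, all under Statistical analysis:
- Student's t, ANOVA and chi-square tests "will be performed to compare the study groups and control group at the baseline".
- Imbalances are described by a mean or relative risk with 95% CI.
- Effect sizes are stratified by GA.

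The Cost analysis section, by contrast, lists covariates for its regression, and GA is among them.

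**The concern.** A change score subtracts the whole of the entry score, which is the right amount only when entry and discharge scores are perfectly correlated (with equal variances). At any lower correlation it over-corrects. This has two consequences.

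- The contrast carries avoidable noise, in a trial with 40 infants per group.
- A group that by chance enters with higher PIPP tends to show a larger fall with no treatment effect, through regression to the mean.

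Testing the groups at baseline does not repair this, because the estimate stays the same whatever the P-value. GA-stratified effect sizes give estimates within strata, not an adjusted primary contrast. A model sentence that gives entry PIPP no role also leaves the choice between an adjusted and an unadjusted contrast open until any imbalance is visible.

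**Working it through.** **Inputs.** From Statistical analysis: "the sample size is computed considering an effect size (f) of 0.30". The same section plans for 80% power at the 5% level, arrives at 37 infants in each group, raises this to 40 (120 in all), and cites PIPP SDs of 2.7, 3.2, 3.4 and 4.5. The entry-discharge correlation r is not in the document, so I assume a range. I also assume equal entry and discharge variances s².

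**1. The plan's own figure.** One-way ANOVA F test, three groups, noncentrality λ = f²N, df 2 and N−3.
- 36 per group: power 79.2%.
- 37 per group: λ = 0.09 × 111 = 9.99, power 80.35%. The stated 37 reproduces.
- 40 per group: λ = 0.09 × 120 = 10.8, power 83.6%.

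**2. Variance with and without adjustment.**
- Change score: 2s²(1−r).
- Adjusted for entry score: s²(1−r²).
- Ratio: (1−r²) / [2(1−r)] = (1+r)/2, which is below 1 for every r < 1.

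**3. Power if f = 0.30 refers to the change score.** The adjusted effect size is 0.30/√((1+r)/2), with one further df spent on the covariate.

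| r | Variance ratio | Variance cut | Adjusted f | n per group for 80% power | Power at 40 per group |
|---|---|---|---|---|---|
| unadjusted | 1 | none | 0.300 | 37 | 83.6% |
| 0.2 | 0.60 | 40% | 0.387 | 23 | 97.1% |
| 0.5 | 0.75 | 25% | 0.346 | 28 | 92.9% |
| 0.8 | 0.90 | 10% | 0.316 | 34 | 87.4% |

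**4. Power if f = 0.30 refers to the discharge score.** The document does not say which score f describes. Here the change score has f = 0.30/√(2(1−r)) and the adjusted analysis has f = 0.30/√(1−r²). Power at 40 per group:

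| r | Change score | Adjusted |
|---|---|---|
| 0.2 | 62.7% | 85.1% |
| 0.5 | 83.6% | 92.9% |
| 0.8 | 99.8% | 99.9% |

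**5. Chance imbalance at entry.** The standard error of a difference in mean entry PIPP between two groups of 40 is SD × √(2/40) = 0.224 SD. The cited SDs come from single procedures, and I assume that they hold at entry.
- SD 2.7: SE 0.60, 95% range ±1.18 points.
- SD 4.5: SE 1.01, 95% range ±1.97 points.

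An entry imbalance of size d shifts the change contrast by (1−r)d in absolute size. At the 95% limit this is 0.83 to 1.38 points at r=0.3, 0.59 to 0.99 at r=0.5 and 0.35 to 0.59 at r=0.7.

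**6. GA.** Its extra gain cannot be computed from the document. The Measures section makes GA a scored PIPP item. If that item is scored from GA at birth (an assumption), it cancels in the change, and any gain would come only through GA's relation to the other items.

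**The case against.** The best defence is that the plan is silent here and has not decided against adjustment. The mixed model's fixed effects are not listed, and a covariate list is often left to an analysis plan, which is not shown. With free group means at entry, the group-by-time contrast equals the raw change. With entry PIPP as a covariate, or a common entry mean, the model behaves like ANCOVA. A change outcome is also compatible with adjustment: regressing change on group and entry score gives the same group estimate and standard error as regressing the discharge score on them.

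This stands in part. It shows that the remedy fits the plan easily, but not that the plan contains it. The article lists covariates for cost and none for the primary outcome.

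A reader might also infer more than the document supports:
- **That the plan rejects adjustment.** It states none, which is weaker.
- **That the primary result would be biased or the sample size wrong.** Randomisation keeps the unadjusted contrast unbiased on average, and 37 per group reproduces.
- **That a change score doubles the noise.** Relative to the discharge score alone, its variance ratio is 2(1−r), which is 2 only at r=0. It is 1.6 at r=0.2 and 1.0 at r=0.5.
- **That GA is ignored.** It is a scored PIPP item, defines strata for effect sizes and is a covariate in the cost model.
- **That the three-group comparison should give way to OMT versus sham.** Nothing here bears on that choice.

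**Conclusion.** The point holds as a matter of efficiency and prespecification in the primary analysis, not as a failure of validity. As written, the primary contrast is an entry-to-discharge change with no stated adjustment. Adjusting for entry PIPP would cut its variance by 40% to 10% for r from 0.2 to 0.8, and would remove the conditional shift from an entry imbalance.

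The size rests on equal entry and discharge variances and on an assumed r. At high r the gain is small. The power gain, from 83.6% to between 87% and 97%, also requires that f = 0.30 describes the change score. If it describes the discharge score and r is low, the unadjusted change falls below the planned 80%. The benefit of adding GA is plausible but not quantified.

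**What to change.** In Statistical analysis, state that the primary three-group PIPP comparison includes entry PIPP as a prespecified covariate. Discharge score or change may be the response, since the group estimate is the same. Name continuous GA as a second prespecified covariate, without claiming a figure for its gain. Report adjusted group differences with 95% confidence intervals. Keep the baseline summaries as description, and do not rely on baseline significance tests to detect or handle imbalance. The cost model already adjusts for GA and needs no change on this point.

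The cost is one or two sentences. Entry PIPP and GA are already collected, the sample size stays as it is, and each covariate uses one degree of freedom.

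### The per-session PIPP outcome names no comparator arm and within-arm analyses are unranked, so a non-specific pre-post shift could be reported as an OMT effect

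*Protocol article*

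**What the plan says.** The Outcomes section lists as its first secondary outcome the "mean difference in PIPP questionnaire scores before and after each" treatment. The length-of-stay, cost and adverse-event items in the same list name a comparison between the three groups or between the two OMT subgroups. The PIPP item does not, and neither does the last item, daily weight gain. The primary outcome is explicitly comparative: "Primary outcome will be the mean difference in baseline score changes of PIPP questionnaire between discharge and entry among the three groups".

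Under Osteopathic procedure, "The sham group will receive only ‘soft touch’, for 30 minutes, plus routine care, whereas the control group will receive routine care only". Sessions are weekly in the two treated arms only: "Osteopathic care and sham therapy will be administered once a week according to the treatment group".

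Under Statistical analysis, "A linear mixed effect model will be used to evaluate the PIPP score across groups", followed directly by "Data will be analysed within and between the three study groups". A general two-sided 0.05 threshold comes later in the same paragraph. Neither kind of analysis is given priority.

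**The concern.** A pre-post test within one arm and a comparison between arms have different null hypotheses. The first asks whether mean PIPP changes across a session. The second asks whether OMT changes it more than sham does. The answers diverge whenever PIPP moves for reasons that have nothing to do with OMT, such as being handled for 30 minutes, settling, or a change of behavioural state, which is itself a PIPP item scored 0 to 3. For a within-arm change from entry to discharge, maturation is a further cause.

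The per-session score is the only listed outcome that looks directly at what a session does to pain, which is the trial's subject. If it is analysed as worded, a significant fall in the OMT arm could be presented as pain relief even if sham infants fell by the same amount. Setting a significant change in one arm beside a non-significant change in another does not repair this, because that is not a test of the difference between them.

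**Working it through.** **1. The plan's own figure.** The sample size for each of the three arms rests on "an effect size (f) of 0.30, a statistical power of 0.80 and an α-level equal to 0.05 to produce a sample size of 37 per" [arm]. For a one-way ANOVA with three groups, the noncentrality is λ = N·f².
- n = 36 per group: λ = 108 × 0.09 = 9.72, power 0.792.
- n = 37 per group: λ = 111 × 0.09 = 9.99, power 0.803.
- n = 40 per group: λ = 120 × 0.09 = 10.8, power 0.836.

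The stated 37 reproduces. It is built on a between-group test.

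**2. Which arms can have the per-session outcome.** OMT and sham infants have weekly sessions, so a before and an after exist. Controls receive routine care only, so neither exists. The only randomised contrast available for this outcome is OMT versus sham, and the article does not name it.

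**3. Inputs for the size of the problem.**
- n = 40 per arm (Statistical analysis).
- Score SDs of 2.7 (non-painful procedure) and 3.2 (simulated handling), both from Statistical analysis.
- Assumed pre-post correlation ρ = 0.5, so the SD of the change is SD × √[2(1 − ρ)] = SD × 1, which is 2.7 to 3.2.
- Assumed: one change score per infant, the same shift δ in every arm, and no OMT effect. The document gives no value for δ.

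**4. Within-OMT test.** A two-sided paired t-test at 0.05 on 39 degrees of freedom has noncentrality δ√40 / SD.

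| Shift δ (points) | Noncentrality, SD 2.7 | Rejects | Noncentrality, SD 3.2 | Rejects |
|---|---|---|---|---|
| 0 | 0 | 0.050 | 0 | 0.050 |
| 0.5 | 1.17 | 0.208 | 0.99 | 0.161 |
| 1.0 | 2.34 | 0.627 | 1.98 | 0.487 |

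**5. OMT-versus-sham test of the same changes.** The common shift cancels. In simulation (20,000 runs) this test rejected in 4.5-5.2% of trials.

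**6. Significant in OMT but not in sham.** With independent arms this has probability p(1 − p). At a 1-point shift that is 0.627 × 0.373 = 0.234 and 0.487 × 0.513 = 0.250. Simulation gave 0.235 and 0.252.

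**7. Cross-check on a standardised scale.** For a common shift of 0.2, 0.3, 0.4 and 0.5 SD of the change, the within-arm test at n = 40 rejects with probability 0.235, 0.457, 0.694 and 0.869. A three-arm ANOVA of the changes stayed at 0.050 to 0.052. A 1-point shift is 1/3.2 = 0.31 to 1/2.7 = 0.37 SD, so the two scales agree.

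**8. Precision of the alternative.** The standard error of a within-arm change is SD/√40, or 0.43 to 0.51 points. For the difference between two arms it is SD × √(2/40), or 0.60 to 0.72 points. The ratio is √2, about 1.4.

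**The case against.** The strongest reply is that the article already contains what is needed. It plans a mixed model of PIPP across groups, not restricted to the primary outcome. It plans between-group as well as within-group analysis, and it has a sham arm with a matching 30-minute weekly session. The phrase 'each treatment' can be read to include sham. A within-infant change is only an endpoint variable, and the comparator can come from the analysis, as it does for the primary outcome. Daily weight gain also lacks a stated comparison, so the omission is weak evidence that an uncontrolled contrast was intended. A journal article may also leave exact secondary contrasts to a fuller document.

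Most of this stands. A reader might infer that the trial will report a within-arm fall as an OMT effect; the article nowhere says so. A reader might also infer that the mixed model cannot help; it can, and the remedy below uses it.

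Two things remain. Unlike the weight-gain item, the PIPP item does state a contrast, and that contrast is before against after. The Statistical analysis section also puts within-group analysis beside between-group analysis without saying which supports a conclusion.

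The rates above are also open to challenge, since they are ordinary paired-test power under assumed shifts. That is correct. The protocol's own PIPP differences, 10.3 − 6.3 = 4.0 and 12.9 − 6.0 = 6.9 points, contrast painful or heel-stick procedures with non-painful or simulated ones. They say nothing about drift over a gentle session.

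**Conclusion.** The point holds in limited form, as a minor one. As worded, the per-session PIPP outcome is an uncontrolled before-after contrast that controls cannot have, and within-arm analyses are not ranked below between-arm ones. A non-specific shift could therefore be reported as an OMT effect. With no OMT effect, a within-OMT test would reject in about 16-21% of trials for a 0.5-point shift and 49-63% for 1 point, against about 5% for OMT versus sham. These rates assume 40 infants per arm, one change score each, an SD of the change of 2.7 to 3.2 and an equal shift in all arms. The real shift is unknown, and weekly repeated sessions would change the rates.

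It would be tempting to extend this to the trial's main result. The documents do not support that: the primary outcome is compared among the three groups, and the sample size reproduces as a between-group calculation.

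**What to change.** - **Outcomes:** define the per-session outcome as the difference between OMT and sham in the before-to-after change in PIPP, scored at the same two times in both arms. State that controls do not contribute.
- **Statistical analysis, model:** estimate this as the arm-by-time (pre/post) term of the linear mixed model already planned, with a random infant effect.
- **Statistical analysis, within-group sentence:** keep within-arm changes as descriptive summaries without P-values, and state that conclusions about OMT rest on between-arm contrasts.

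The cost is the rewording of one secondary outcome and one analysis sentence, with no extra infants. PIPP has to be scored around sham sessions as well as OMT sessions. The between-arm contrast is less precise, with a standard error about 1.4 times that of the within-arm change.
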